### Primary hypotheses and outcomes

1. MICA will increase the initiation of highly effective contraceptives in jail more than educational videos. The primary outcome is initiation of a highly effective contraceptive method prior to release from jail. This will be measured by a review of the medical records and documentation of participants having received a contraceptive injection, pills, patch, ring, or other contraceptive device. Type of contraceptive and amount given will be recorded.

2. Women randomized to MICA will be more likely to continue the use of highly effective contraception at 3, 6, 9, and 12 months compared to women randomized to educational videos. The primary outcome is continued highly effective contraceptive use at 3, 6, 9, and 12 months. This will be measured through the TLFB calendars and confirmed with a review of the medical records. The secondary outcome is pregnancy as documented by a urine pregnancy test at each follow-up visit.

3. MICA will more effectively decrease unsafe sexual behavior more than educational videos. The primary outcome is an incident STI after a negative baseline test. The secondary outcome is intercourse that is poorly protected against STIs at 3, 6, 9, and 12 months as determined by the TLFB.

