### Participants

Participants will be recruited from the Rhode Island Department of Corrections (RI DOC) women’s division. All women between the ages of 18 and 35 years will be approached by a research assistant for study participation and after obtaining verbal consent will be screened for eligibility. This screening visit and all subsequent visits occur in a private location and study participation is not discussed with security staff.

Inclusion criteria include: (1) 18 to 35 years of age; (2) currently sexually active with men defined as having vaginal-penile intercourse at least monthly in the past three non-institutionalized months; (3) answered ‘No’ to ‘Do you plan to become pregnant within the next 12 months?’ (4) expected place of residence after release in Providence County or within 15 miles of follow-up site; (5) willing to comply with protocol, follow-up, and provide at least one locator; and (6) fluent in English.

Exclusion criteria include: (1) inability to give informed consent secondary to organic brain dysfunction, not having own legal guardianship, or active psychosis or otherwise unable to participate in the intervention or assessments (deaf, blind, or impaired communication skills that impair ability to participate in computerize assessment or counseling); (2) pregnant or trying to become pregnant within the next year; (3) hysterectomy, bilateral oophorectomy, tubal sterilization (by ligation or coils), intrauterine device (IUD), implantable contraceptive devices (Implanon) or other procedures which make it extremely unlikely to become pregnant; (4) women who are monogamous for more than 1 year with a partner who has had a vasectomy; (5) housed in segregation as we would be unable to recruit them for the study (once released from segregation a woman would then become eligible).

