Before the first intervention session, a 45-60-minute computer-assisted questionnaire will be administered to the participant. From the baseline questionnaire, we will gather the following information: demographics, obstetric and gynecologic history, length of stay in prison, medical insurance, primary care provider or clinic, relationship violence, childhood abuse, addiction, and depression. These measures will aid in assessing the complex context in which a woman ‘chooses’ to initiate or not initiate contraceptive services.

The counselor/RA will then administer MICA or video according to randomization. Self-obtained vaginal samples for *Trichomoniasis vaginalis *, *C. trachomatis*, and *N. gonorrhoeae* will be obtained as well as a urine sample for a pregnancy test. Contraceptive, sexual, and drug-related risk behaviors will be measured via a calendar recall behavioral assessment, a Timeline Followback (TLFB) calendar of the prior 90 days at baseline and at each follow-up visit
[36,37]. This assessment utilizes a calendar-based recall method using anchor dates to facilitate a more accurate response set. It also allows for a more thorough assessment of risk behaviors by allowing for the analysis of risk patterns by sexual partner, drug, and alcohol use and the co-occurrence of sexual- and drug-related risk, all within the context of life events. A detailed assessment of sexual behaviors and condom use with each of the participant’s other sex partners will be made by the participant.

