#### *VIDEO*

Participants randomized to control videos will watch information on contraception and STI prevention that a participant would need to avoid exposure to intercourse that is poorly protected against pregnancy and against STIs. The baseline video is about contraception and is matched in time to the MICA sessions. At the 3-month post release session the video focuses on STIs, condom use, and preconception counseling.

At the end of the MICA or video session, the counselor will offer participants a list of community-based locations at which contraceptive services and STI screening can be accessed inexpensively or for free. Each participant will also be offered a referral to the Title X reproductive health educator at the jail. (In conjunction with RI DOC, the Title X program provides reproductive health services in jail and then transitional services in the community after release.) On-site contraceptive options include oral contraceptive pills, contraceptive patches, vaginal rings, and medroxyprogesterone injections. The counselor will suggest that the participant visit her primary care provider, the prison physician or one of the sites on the list for contraceptive supplies, annual pelvic examinations, and regular STI screening.

Follow-ups will occur at 3, 6, 9, and 12 months post release in the community or prison if re-incarcerated. This is a challenging population to track and retain in a longitudinal study. However, we have refined methods for tracking participants as they re-enter the community. In our previous trials, including Project WISE (PI [name] R01DA024093), we have been able to locate and retain over 80% of participants for their follow-up assessments. Participants are asked to sign a letter for all locators that explains that they are participating in a research study and gives their permission to provide the study staff with information about the participant’s whereabouts if needed. Prior to each follow-up assessment, study staff attempt to contact participants to remind them of the appointment by letters and phone calls. The participant is asked to review and confirm or edit contact information at each visit. Financial compensation for the time and effort to provide assessment information and biologic samples also aids in study retention.

Questionnaire measures include contraceptive use, barriers to family planning services, relationship violence, substance use, depressive symptoms, pregnancy intentions and plans

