### Statistical analyses

#### *Primary analyses*

Data analyses will be performed using the Statistical Analysis System, SAS 9.1.3 (SAS Institute, Inc, Cary, NC, USA). Following intention-to-treat principles, all participants who have been randomized to the two interventions will be included in the analyses. All significance tests will be two-tailed.

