#### *Contraceptive initiation (Aim #1)*

Analyses of contraceptive initiation while incarcerated will include the percentage of participants starting a highly effective method requiring infrequent user maintenance (Subdermal implant, injectable contraception, or an IUD) as well as highly effective methods requiring more regular non-coital use (contraceptive pills, vaginal rings, and the patch). Initiation of contraception use (yes/no) will be analyzed using logistic regression to determine if women randomized to the MICA condition are more likely to initiate a contraceptive method while incarcerated than women randomized to the video condition. Baseline randomization characteristics (for example, age, race/ethnicity, and pregnancy intentions) will be incorporated in the initial model to insure randomization was successfully accomplished. Odds ratios and their 95% confidence intervals will be calculated for MICA using the video condition as the referent.

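### The Aim 1 measure does not separate a new start from resupply in eligible current users, and neither contraceptive model names baseline use

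*Protocol article*

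**What the plan says.** All places are in the Protocol article.

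- **Outcome label** (Primary hypotheses and outcomes, item 1): "The primary outcome is initiation of a highly effective contraceptive method prior to release from jail". The Aim 1 analysis section likewise speaks of the "percentage of participants starting a highly effective method requiring infrequent user maintenance" and adds the pill, ring and patch.
- **Measurement** (same item): medical-record review and "documentation of participants having received a contraceptive injection, pills, patch, ring, or other contraceptive device". Type and amount are also recorded.
- **Entry** (Participants): the exclusions cover sterilisation, "intrauterine device (IUD), implantable contraceptive devices (Implanon) or other procedures which make it extremely unlikely to become pregnant". Pill, patch, ring and injection users are not listed.
- **Supply in jail** (VIDEO): "On-site contraceptive options include oral contraceptive pills, contraceptive patches, vaginal rings, and medroxyprogesterone injections".
- **Analysis set** (Primary analyses): "all participants who have been randomized to the two interventions will be included in the analyses".
- **Models**: for Aim 1, "Initiation of contraception use (yes/no) will be analyzed using logistic regression", with the randomisation characteristics (age, race/ethnicity, pregnancy intentions) as covariates. For Aim 2, the mixed model has treatment, intentions, time, education, insurance, alcohol/drug use and pregnancy history.
- **Baseline data** (Procedures/Interventions): contraceptive behaviour is taken from a TLFB "calendar of the prior 90 days at baseline and at each follow-up visit".

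**The concern.** The hypothesis is about starting a method, while the measure records receiving one. The methods not excluded at entry are the same four that the jail dispenses, so a woman who arrives on the pill and has her supply continued can meet the measure in either arm. All randomised women are analysed, so she stays in both numerator and denominator.

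Aim 3 deals with the parallel problem: an incident STI counts only if the woman tested negative at baseline. Aim 1 has no corresponding baseline condition.

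At stake are the meaning of the first primary outcome and its power. Events that would occur at the same rate in both arms carry no information about MICA and pull the comparison toward no difference. Separately, prior use is likely to be a strong predictor of both contraceptive outcomes. Leaving it out of the named covariates gives up precision that the trial has already paid to collect.

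**Working it through.** **The plan's own figure.** The only sized outcome is the 12-month STI rate, 43% versus 31%, two-sided α 0.05, power 80%. The two-proportion formula is n = [1.96·√(2·0.37·0.63) + 0.84·√(0.43·0.57 + 0.31·0.69)]² / 0.12², which gives 253 per arm. The factor for four measures with correlation 0.50 is (1 + 3·0.5)/4 = 0.625, and 253·0.625 = 158.1. Allowing 20% attrition, 158.1/0.80 gives 198 per arm, or 396 in total against the stated 400. The figure reproduces, but it says nothing about Aim 1, for which the article gives no rates and no power.

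**Dilution in Aim 1.** Let f be the share of current users in each arm, r the proportion of them with a supply recorded in jail (the same in both arms), and p the initiation rate among non-users. Then:

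- arm rate = f·r + (1 − f)·p
- risk difference as measured = (1 − f) × risk difference among non-users

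The term f·r cancels, so the second line holds for any r.

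**Assumed inputs** (none is in the article): p = 30% video and 44% MICA, and r = 90%. From the article: 200 per arm and two-sided 0.05. Example at f = 10%:

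- video: 0.10·0.9 + 0.90·0.30 = 0.360
- MICA: 0.10·0.9 + 0.90·0.44 = 0.486
- difference: 0.126 = 0.90·0.14
- power: Φ[(0.126 − 1.96·√(2·0.423·0.577/200)) / √((0.36·0.64 + 0.486·0.514)/200)] = Φ(0.595) = 0.72

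The restricted analysis keeps 30% versus 44% with 200·(1 − f) women per arm.

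| f | Video | MICA | Difference (points) | OR | Power as written | Non-users per arm | Power restricted |
|---|---|---|---|---|---|---|---|
| 0% | 0.300 | 0.440 | 14.0 | 1.83 | 0.83 | 200 | 0.83 |
| 5% | 0.330 | 0.463 | 13.3 | 1.75 | 0.78 | 190 | 0.81 |
| 10% | 0.360 | 0.486 | 12.6 | 1.68 | 0.72 | 180 | 0.79 |
| 20% | 0.420 | 0.532 | 11.2 | 1.57 | 0.61 | 160 | 0.74 |

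**Sensitivity to the assumptions.**

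- With r = 50%, power as written is 0.74 at f = 10% and 0.63 at f = 20%. With r = 30% it is 0.75 at f = 10%. All are below the restricted values.
- With 30% versus 45% and r = 100%, power as written versus restricted is 0.83 versus 0.86 (f = 5%), 0.78 versus 0.84 (10%) and 0.67 versus 0.79 (20%).
- With 20% versus 32% and r = 100%, it is 0.50 versus 0.69 at f = 20%.
- If current users were never scored as events (r = 0) but stayed in the denominator, 30% versus 45% at f = 20% gives 0.75, against 0.79 restricted. A new-start rule without restriction therefore recovers only part of the loss.

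**Baseline-use covariate.** These simulations assume that baseline use multiplies the odds of the outcome by 8. With 25% baseline users, one run of 400 women (treatment OR 1.85, 1,500 replicates) raised power from 0.74 to 0.81, and a second run from 0.70 to 0.79. With 10% baseline users, power rose from 0.78 to 0.81. These are indicative only.

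**The case against.** A reader might infer that the protocol counts current users as initiators. It does not say so. The outcome is called initiation, the analysis speaks of starting, and the phrase about methods received can be read as naming the evidence for an initiation. The article is silent on resupply in both directions, and one can argue that such a coding rule belongs in a fuller document. This stands against any claim of a misstatement. It does not remove the point, because the article does fix the measure, the eligible population, the analysis set and the named covariates, and together these leave new starts and resupply unseparated.

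A reader might also infer bias in favour of MICA. That is not supported either: randomisation balances current users on average, and the effect is attenuation. If MICA also raised resupply among current users, the dilution would be smaller.

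Omitting a prognostic covariate does not invalidate a randomised comparison, and the Aim 1 covariate list is introduced as examples. Under Aim 2 a woman who continues her method is correctly scored, so only precision is at issue there. This stands.

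The share of current users is unknown. The Background reports that over three-quarters of at-risk women in jail want to start a method, which hints that the share may be limited without giving it.

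Finally, the article does not state that the TLFB precedes the opening of the allocation envelope, so a TLFB-defined subset is not assured to be a pre-randomisation one. The worry is limited, since the calendar recalls the prior 90 days and is reviewed within the first MICA session, but the order should be fixed.

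**Conclusion.** The point holds in this form: as written, the Aim 1 measure does not distinguish a new start from resupply in current users, who are eligible, and neither contraceptive model names baseline use although it is collected. The direction is firm if current users score alike in both arms: the risk difference shrinks by (1 − f), and in every scenario shown the odds ratio moves toward 1.

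The size rests on assumed rates and an unknown f. In the main scenario the restricted analysis gains 0.03 in power at 5% current users, about 0.06 to 0.07 at 10% and 0.13 at 20%. It does not return to 0.83, because restriction itself costs 0.83 − 0.74 = 0.09 at 20%. The matter is worth correcting because it bears on what the first primary outcome means. It does not threaten the validity of the randomised comparison, and it does not concern Aim 3.

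**What to change.** 1. Define Aim 1 initiation as receipt in jail, before release, of a highly effective method not in use before incarceration, taking prior use from the part of the baseline TLFB that precedes incarceration.
2. Analyse Aim 1 among baseline non-users, and report alongside it the analysis of all randomised women adjusted for baseline use. Adjustment alone does not repair the outcome definition.
3. Add baseline highly effective contraceptive use as a named covariate in the Aim 1 logistic model and the Aim 2 mixed model.
4. Complete the baseline TLFB before the allocation envelope is opened, so that the subset is defined before randomisation.

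The data are already planned, so items 1 to 3 change wording and item 4 changes the order of baseline procedures. The real cost is a smaller Aim 1 denominator: 200·(1 − f) per arm, for example 180 at 10% current users and 160 at 20%. Restriction also departs from the stated all-randomised analysis, which is why that analysis should be kept alongside.

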### Sample size

The sample size calculation is based on the biological outcomes and is the most conservative estimate. Data from our prior work (project CONNECT
[20]) shows that the 6-month incidence of an STI was 33%
[38]. We assume over a 12-month period this will increase to 43%. From this data, we assume that the intervention will decrease the incidence a moderate amount to 31%. Similarly, we assume a type I error of α = 0.05, an average within-subject correlation of 0.50 and a conservative estimate of a 20% attrition rate
[39]. Using the similar procedure as above, the proposed enrollment of 400 participants (200 participants for each intervention) at baseline will achieve power of 80% to detect assumed differences after considering four repeated measures (3, 6, 9, and 12 months). Our proposed sample size may provide greater power to detect interaction effects, robustness to violations of model assumptions, protection against multiple comparison error rates, and increased efficiency to detect weaker relationships between variables.

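### The stated 80% power for incident STI does not follow from 43% versus 31% at 12 months; those inputs give about 60%

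*Protocol article*

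**What the plan says.** All inputs are in the protocol article.

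- **Source rate (Sample size).** The sponsor's earlier study "shows that the 6-month incidence of an STI was 33" per cent.
- **Control risk (Sample size).** "We assume over a 12-month period this will increase to 43" per cent.
- **Intervention risk (Sample size).** "we assume that the intervention will decrease the incidence a moderate amount to 31" per cent.
- **Other assumptions (Sample size).** "we assume a type I error of α = 0.05", within-subject correlation 0.50, attrition 20%, 200 women enrolled per arm.
- **Result (Sample size).** This enrolment "will achieve power of 80% to detect assumed differences after considering four repeated measures (3, 6, 9, and 12 months"). The section calls the estimate the most conservative one. It adds that the size may also give "protection against multiple comparison error rates".
- **Outcome (Primary hypotheses and outcomes, item 3).** "The primary outcome is an incident STI after a negative baseline test".
- **Test (Primary analyses).** "All significance tests will be two-tailed".
- **Model (Incident STIs, Aim #3).** A generalized linear mixed model over the follow-up visits. No per-visit STI risk is given anywhere.

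**The concern.** A figure that grows from 33% at 6 months to 43% at 12 months is a cumulative risk. A woman either has or has not had an incident STI by month 12, and that result cannot be observed four times. Repeated measures add information only about a quantity that is measured anew at each visit, such as the risk in each 3-month interval, and that risk must be smaller than the 12-month risk it builds up to. Taking the 12-month percentages and also the gain from four visits counts the same events more than once.

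This calculation fixes the enrolment of 400. A reader who trusts 80% power would take a null STI result as fair evidence against a 12-point reduction. If the true power is near 60%, that inference is much weaker.

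**Working it through.** **Inputs.** p1 = 0.43, p2 = 0.31, difference d = 0.12, mean p = 0.37; alpha 0.05 two-sided (z = 1.96); 200 per arm × (1 − 0.20) = 160 completers per arm; correlation ρ = 0.50; m = 4 visits.

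**Formula (two proportions, pooled variance under the null).**
Power = Φ{ [d − 1.96·√(2·0.37·0.63/n)] / √((0.43·0.57 + 0.31·0.69)/n) } = Φ{ [0.12 − 1.96·√(0.4662/n)] / √(0.4590/n) }

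**Step 1. Reproduce the plan's figure.**
- Repeated-measures variance factor: (1 + (m − 1)ρ)/m = (1 + 3 × 0.5)/4 = 0.625.
- Effective n = 160/0.625 = 256 per arm.
- Power = Φ[(0.12 − 1.96 × 0.04267)/0.04234] = Φ(0.859) = 0.805.
- In reverse: 80% power needs 253 per arm; 253 × 0.625 = 158; 158/0.8 = 198 per arm, about 395 in total, against the stated 400.

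Every stated input is used, and both the 80% and the 400 come back.

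**Step 2. One 12-month outcome per woman.**
- n = 160: Φ[(0.12 − 1.96 × 0.05398)/0.05356] = Φ(0.265) = **0.605**.
- n = 200 (no attrition): Φ[(0.12 − 1.96 × 0.04828)/0.04791] = Φ(0.530) = 0.702.
- Other approximations at n = 160: unpooled 0.610, arcsine 0.606, logit 0.601, continuity-corrected 0.559.
- Time to first STI (log-rank): hazard ratio ln(0.69)/ln(0.57) = 0.660, events 160 × (0.43 + 0.31) = 118, power 0.618.

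**Step 3. Four visits, with per-visit risks that agree with the 12-month figures.** Under a beta-binomial model with per-visit risk p and correlation ρ > 0, set θ = (1 − ρ)/ρ, a = pθ, b = (1 − p)θ. Then P(no STI at any of four visits) = product over j = 0 to 3 of (b + j)/(a + b + j). At ρ = 0 it is (1 − p)^4. Solve for the p that gives 12-month risks of 0.43 and 0.31, then apply the variance factor to 160 per arm.

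| ρ | Per-visit risks | Effective n per arm | Power |
|---|---|---|---|
| 0 | 0.131 vs 0.089 | 640 | 0.68 |
| 0.1 | 0.151 vs 0.102 | 492 | 0.64 |
| 0.3 | 0.194 vs 0.132 | 337 | 0.60 |
| 0.5 (the plan's value) | 0.246 vs 0.168 | 256 | 0.59 |

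**Step 4. The converse check.** If 43% were the risk at each visit with ρ = 0.50, the 12-month incidence would be 66% under the same model. Without that model, an equal risk of 0.43 at each visit and pairwise correlation 0.50 allow anything from 55% to 80%. None of these is 43%.

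**Step 5. What 160 per arm can detect, and what 80% would need.** 43% versus 28% at n = 160 gives power 0.80. For 43% versus 31%, 253 evaluable women per arm are needed: 253/0.8 = 316.25, so 317 per arm or 634 in total.

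**Step 6. Sensitivity to the baseline-negative requirement (assumption).** The documents give no baseline-positive share. If 10% to 30% of the 160 were excluded for that reason, n would be 144 to 112 and the Step 2 power 0.56 to 0.46.

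**The case against.** **The formula is not shown.** The section refers to a procedure described above that the article does not contain. This stands: Step 1 is a close reconstruction, not proof of how the sponsor calculated. A one-sided test with 200 per arm and no attrition also gives 0.802, but it conflicts with the two-tailed tests, the 20% attrition and the four repeated measures. The discrepancy does not depend on the mechanism, because no reading tried that keeps the two-sided test, the attrition and the 12-month meaning of the percentages reaches 80%.

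**The planned analysis is a mixed model over visits.** Repeated observations are legitimate here, and the error is not their use. It is the pairing of 12-month percentages with visits. About 60% therefore belongs to the single 12-month comparison, and 59% to 68% to the repeated-measures analysis under the model in Step 3.

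**Stronger readings that the documents do not support.**
- *Power as low as 34%.* This pairs 13.1% versus 8.9% with ρ = 0.50. Those risks match 43% and 31% only at ρ = 0. At ρ = 0.50 the Step 3 model turns 13.1% into about 25% at 12 months.
- *A 40% to 50% chance of missing the effect.* The upper end needs a baseline-positive share that is not documented. Nor is it known whether the 33% was already measured among baseline-negative women.
- *A flat 66% cumulative incidence.* That value depends on the model; only the direction is general.
- *A failure to adjust for three primary outcomes.* The outcomes serve three separate aims, and a multiplicity strategy may sit in an analysis plan that is not shown. Judging the power at a divided alpha would apply a correction that the article does not adopt.

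**Conclusion.** The power statement is wrong as written. With the stated risks, two-sided alpha 0.05 and 160 completers per arm, a single 12-month comparison has about 60% power (70% with no attrition). A repeated-measures analysis on consistent per-visit risks has about 59% to 68%. The chance of missing the assumed 12-point effect is about 40%, twice the 20% implied. It would be higher if baseline-positive women have to come out of the 160, by an amount that cannot be fixed from the documents.

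The conclusion rests on reading 43% and 31% as cumulative 12-month risks, which the section's own wording requires, and on the independence or beta-binomial models for the repeated-measures range. Type I error and the validity of the effect estimate are not affected. The consequence is for how a null STI result may be read, and it concerns one of the three primary outcomes, but it is the one on which the trial was sized.

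The remark on multiple comparisons is a smaller fault in the same paragraph: a larger sample raises power but does not control type I error.

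**What to change.** Replace the power sentence in Sample size with, for example: *With 160 evaluable women per arm, a 12-month incidence of 43% versus 31% gives about 60% power; 80% power is available for 43% versus about 28%.* Alternatively, keep a repeated-measures calculation but state the per-visit risks and correlation, and show that they reproduce the assumed 12-month incidences. In either case, say whether the 160 already excludes baseline-positive women and, if not, deduct their expected share. Delete the phrase that credits the sample size with protection against multiple-comparison error.

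The cost is a few sentences and a less favourable stated power. Enrolment, outcomes and analysis model stay as they are, which matters because the Trial status section says that recruitment is already under way.

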#### *Contraceptive continuation (Aim #2)*

Analyses of contraceptive continuation will include the assessment of highly effective contraception use (yes/no) at the four follow-up time points. In addition to assessment of contraception use, pregnancy intentions will also be assessed at each time point. Generalized linear mixed models (GLMM) will be used to analyze the binary outcome. GLMM allows for flexibility in the distribution of the outcome and can also incorporate repeated measures of both dependent and independent variables. Independent variables in the GLMM will include treatment group, pregnancy intentions, an indicator variable for time as well as risk factors for unplanned/unwanted pregnancy (education, health insurance status, alcohol/drug use, and pregnancy history). Testing the interaction between treatment group and time will inform us whether differences in contraceptive outcomes between treatment conditions become more or less pronounced over the 12-month follow-up.

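### Three unranked primary outcomes have no control of family-wise error; the sample size credited with protecting against multiple comparisons cannot do so

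*Protocol article*

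**What the plan says.** Under Primary hypotheses and outcomes, the protocol article lists three hypotheses, each with its own primary outcome. The first is initiation of a highly effective method before release. For the second, "The primary outcome is continued highly effective contraceptive use at 3, 6, 9, and 12 months". The third is a new STI after a negative baseline test. The article does not rank the three, split alpha among them, set a test order or require all three to succeed.

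The Sample size section is built on the STI outcome, which it presents as the most cautious basis. There "we assume a type I error of α = 0.05, an average within-subject correlation of 0.50", with 20% attrition, and 400 women "will achieve power of 80% to detect assumed differences after considering four repeated measures (3, 6, 9, and 12 months"). The section closes with a list of further benefits that the sample size may bring. One of them is "protection against multiple comparison error rates, and increased efficiency to detect weaker relationships between variables".

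Under Primary analyses, "All significance tests will be two-tailed". Aim 1 is a logistic regression reported with 95% confidence intervals. Aim 2 is one generalized linear mixed model (GLMM) over the four visits, for which the article says "Testing the interaction between treatment group and time will inform us" whether the group difference grows or shrinks over follow-up. Aim 3 follows a similar procedure.

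**The concern.** The closing phrase in Sample size credits enrolment with a property it does not have. More participants raise the power of each test. They leave each test's type I error at its nominal level, so the chance of a false positive somewhere among several tests does not fall.

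This matters because the phrase is the only multiplicity provision in the article. With three primary outcomes of equal standing, a reader could take it to mean that no adjustment is needed. A favourable result on any one aim could then be presented as a primary finding at the 5% level, when the chance of at least one such result under no effect is nearly three times that.

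The phrase has a more reasonable meaning: that the trial has enough spare power to bear a stricter alpha. That can be checked for the outcome on which the trial was sized.

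**Working it through.** **Inputs (protocol article, Sample size and Primary analyses).** STI incidence over 12 months 43% (video) and 31% (MICA); two-sided alpha 0.05; power 80%; within-subject correlation 0.50; four repeated measures; attrition 20%; 200 women per arm, hence 200 × 0.80 = 160 completers per arm.

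**Assumption.** The article does not print its formula. I used the usual two-proportion formula and the equal-correlation factor for the mean of four measures, (1 + 3 × 0.50)/4 = 0.625. Whether that factor suits a cumulative incidence is a separate question; it is used here because it reproduces the plan's figure.

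**Step 1: reproduce the 400.**
- Mean proportion 0.37; pooled variance term 2 × 0.37 × 0.63 = 0.4662; unpooled term 0.43 × 0.57 + 0.31 × 0.69 = 0.4590.
- n = (1.960 × √0.4662 + 0.842 × √0.4590)² / 0.12² = 253 per arm.
- 253 × 0.625 = 158.1; divided by 0.80 this is 198 per arm, or 396 in total, against the stated 400.
- In reverse, 160 completers act like 160/0.625 = 256 per arm, and power is 80.5%.

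The stated sample size is therefore reached with the whole of the unadjusted 0.05 spent on the STI outcome.

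**Step 2: family-wise error for three tests at 0.05.**
- Independent tests: 1 − 0.95³ = 14.3%.
- Upper bound under any dependence: 3 × 0.05 = 15%.
- Test statistics correlated at 0.5 (an assumed value): about 12.5% by simulation.

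**Step 3: does sample size change it?** Simulation of three independent two-proportion tests at 0.05 under no effect, with 43% in both arms:

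| Per arm | At least one false positive |
|---|---|
| 160 | 13.8% |
| 200 | 13.9% |
| 1000 | 14.2% |

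A roughly sixfold larger trial gives no protection.

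**Step 4: is there spare power for a stricter alpha on STI?** At 0.05/3 = 0.0167 (critical value 2.394), with 256 effective participants per arm:
- Standard errors: √(0.4662/256) = 0.04267 pooled; √(0.4590/256) = 0.04234 unpooled.
- Pooled variance under the null: Φ[(0.12 − 2.394 × 0.04267)/0.04234] = Φ(0.42) = 66.3%.
- Unpooled variance throughout: Φ(0.12/0.04234 − 2.394) = Φ(0.44) = 67.0%.

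Keeping 80% power at 0.0167 would take 338 × 0.625 = 211.25 completers per arm. Divided by 0.80, that is 265 per arm or 530 in total, against the planned 400.

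**The case against.** The strongest reply is that this is a condensed article. Alpha splits, test orders and adjustments commonly sit in a full protocol or SAP, and their absence here is no fault. That stands, and the point does not rest on absence. The article does address multiplicity, and what it says is wrong.

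It is also fair that the wording is only that the size may provide protection, that no analysis section relies on it, and that no section says each aim is tested at 0.05. The last is inferred from the only alpha stated, the two-tailed rule and the 95% intervals for Aim 1. Nor does the article say that success on any one aim makes the trial positive, and whether distinct aims need joint error control is partly a matter of judgement.

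Four stronger readings are tempting, and the article does not support them:
- **Six primary tests, with a family-wise error near 26%** (1 − 0.95⁶ = 26.5%). This counts the four continuation visits as separate tests. The article puts them in one GLMM and announces no visit-by-visit testing.
- **Power of about 44% after adjustment.** This figure drops the repeated-measures factor. Without that factor, power is already only about 60.5% at unadjusted 0.05, so most of the fall from 80% has nothing to do with multiplicity.
- **No reserve on any outcome.** This is shown only for STI. The article calls the STI calculation the most cautious, which leaves room for higher power on Aims 1 and 2, but gives no figure.
- **The treatment coefficient covers only a reference visit.** This would follow if the interaction stayed in the primary model under reference coding. Neither is stated, and the article describes correctly what an interaction test shows.

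**Conclusion.** The point holds in limited form. The claimed protection does not exist, and the article puts nothing else in its place for three unranked primary outcomes. If each is tested at two-sided 0.05, the chance of at least one false positive when MICA affects none of them is about 14% under independence and at most 15%, against the 5% assumed.

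The spare-power reading fails for the STI outcome, where power is about 80% at 0.05 and about 66–67% at 0.0167, depending on the variance convention. That rests on the reconstructed formula, which comes within four women of the stated 400. Nothing can be concluded about power for Aims 1 and 2. The error is one of wording and analysis specification; it does not invalidate the design.

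**What to change.** 1. In Sample size, delete only the phrase on multiple comparisons. The other benefits listed in that sentence are not at issue here.
2. Under Primary analyses, state that the three primary p-values are tested by Holm's procedure at overall two-sided 0.05: the smallest against 0.0167, the next against 0.025, the last against 0.05, stopping at the first failure. Holm holds under any dependence among the three.
3. Holm needs one p-value per aim. For continuation and incident STI, name the treatment contrast averaged over the four visits as the primary test. Keep the treatment-by-time interaction and visit-specific effects as supportive.
4. State that the 80% power refers to the STI outcome at unadjusted 0.05, and that it is about 66–67% if STI must be tested at 0.0167. Under Holm that is a floor, because STI is tested at 0.025 or 0.05 once other aims have been rejected.

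The cost is a change of wording and a stricter first hurdle: unless the smallest p-value is below 0.0167, no primary claim can be made. No change to enrolment or data collection is needed if the lower STI power is accepted.
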